### Safety, adverse event reporting, and harms

Each safety issue will be defined when one or more of the following respective criteria are met. Intraoperative complications include bowel, ureter, and bladder injuries related to surgical technique. Postoperative complications referred to surgical site infection within 14 days, and unplanned secondary surgery associated with this surgery.

Adverse events are defined as all undesirable symptoms that may have a potential association with the investigational procedures. All adverse events are shared with the investigators and will be dealt with timely and appropriate. Serious adverse events related to this trial will be reported to the Chengdu Women’s and Children’s Central Hospital Certified Review Board (CRB) within 10 days.

### Sample size estimation

The sample size calculation was based on the changes in patients' blood pressure at the beginning of surgery. Since no similar studies have been conducted before, a pilot study was conducted previously. According to the results of the pilot study, in the traditional vNOTES group, 50% of patients had a greater than 20% change in blood pressure at the beginning of the CO_2_ pneumoperitoneum. Due to the different surgical strategies, CO_2_ pneumoperitoneum is not required in the gasless vNOTES group. We assume that the number of patients with a blood pressure change of more than 20% is less in the gasless vNOTES group than in the traditional vNOTES group. The 10% reduction in the gasless vNOTES group was considered to be statistically significant. A statistical power of 80% and a one-sided α significance level of 0.05 were used for power analysis with 1:1 allocation. A sample size of 49 patients in each arm was estimated. Considering a dropout rate of 20%, 60 patients for each group were enrolled.

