## Background

Since Transvaginal Natural Orifice Transluminal Endoscopic Surgery (vNOTES) was applied and reported in 2007 by Marescaux et al., this technique has been increasingly conducted in the field of gynecology, such as hysterectomy [1, 2], adnexectomy [3], and myomectomy [3, 4]. Published literature has proved that, compared to traditional laparoscopic surgery, vNOTES hysterectomy is associated with a lower pain score after surgery and a shorter length of hospital stay [1]. Due to its minimally invasive and without abdominal incisions, maximum aesthetics can be achieved.

During the routine vNOTES procedure, carbon dioxide (CO_2_) pneumoperitoneum is required. CO2 insufflation may induce hemodynamic instability and acid–base imbalance. A well-summarized review has reported that acidosis, inflammation, oxidative stress, and hypothermia may all be associated with CO_2_ pneumoperitoneum [5]. Moreover, in an animal study, the authors found that an inflammatory response was evoked during pneumoperitoneum [6]. Additionally, the transvaginal insertion of devices to establish CO_2_ pneumoperitoneum makes the already narrow surgical space even more crowded, further exacerbating the inconvenience of transvaginal operations [7]. In 2014, Chen et al. performed the first transvaginal appendectomy under gasless laparoscopy [7]. Subsequently, they reported that transvaginal salpingo-oophorectomy with gasless laparoscopy was successfully conducted in ten patients [8]. However, technical difficulties associated with gasless laparoscopy, such as limited abdominal space and poor surgical visualization restrict its application.

To date, literature regarding the advantages of gasless vNOTES is insufficient. Most studies related to gasless vNOTES are case series, which is not convincing enough. Thus, the aim of our study is to compare gasless vNOTES vs. traditional vNOTES on hemodynamic profiles and outcomes in patients with benign gynecological disease. The primary outcome is the changes in mean arterial pressure (MAP) and heart rate (HR) at different time points during the surgery. The secondary outcomes will be surgical conversion rate and complications. We hypothesize that compared with those in the traditional vNOTES group, hemodynamic profiles will be changed less during gasless vNOTES, while safety can be promised.

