### Outcome measures

1. The primary outcome is vital signs at the different time points, including before anesthesia (baseline: T0), at endotracheal intubation (T1), 10 min after endotracheal intubation (T2), at the beginning of the operation (T3), 10 min after the operation (T4), 10 min before the end of the operation (T5), at the end of the operation (T6) and at the time of tracheal extubation (T7).2. The second outcomes are collected as follows.①Surgical conversion rate refers to the surgeon cannot complete the surgery in the scheduled mode of operation, and has to convert to open abdominal surgery or traditional multiport laparoscopic surgery, or single port laparoscopic surgery. For the patient who is allocated to the gasless vNOTES group, the surgeon requires the use of traditional vNOTES with CO_2_ pneumoperitoneum if they are unable to complete the surgery under gasless vNOTES, and this patient is considered as a surgical conversion. If the operation cannot be completed according to the scheduled surgical method, the surgical strategy can be changed as appropriate.② Duration of surgery (from speculum placement to suturing the wound)③ Duration of anesthesia (from anesthesia induction to endotracheal extubation)④ The anesthetic consumption during the surgery, including sufentanil and cisatracurium⑤ Intraoperative estimated blood loss⑥ VAS and PONV scores at postoperative 2 h and 24 h.⑦ Administration of vasopressor drugs from the beginning of general anesthesia induction to 15 min after endotracheal intubation, including times, dosage, and type.⑧ Intraoperative and postoperative complications (e.g., bowel, ureter, and bladder injury, surgical site infection, and unplanned secondary surgery).⑨ Time of first getting out of bed after surgery⑩ Time of first eating after surgery after surgery, including light drink.

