### Statistical methods

Data will be analyzed by using R studio 4.2.2 for Windows (Armonk, NY, United States). Data from the primary outcome will be presented as mean ± standard deviation if normally distributed, and t-test will be conducted; otherwise, the data will be reported as median (IQR), and no-parametric tests will be performed. Categorical data will be summarized as frequencies (percentages) and compared between study groups using χ2 tests or Fisher exact tests, as appropriate. *P* value < 0.05 was considered significant.

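### The stated 80% power belongs to a responder proportion that is not a listed outcome; the primary analysis as planned has no power statement

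*Protocol article*

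**What the plan says.** All references are to the protocol article.

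- **Sample size estimation:** "The sample size calculation was based on the changes in patients' blood pressure at the beginning of surgery". The control figure is a pilot rate seen as insufflation began: "50% of patients had a greater than 20% change in blood pressure". The effect is worded as "The 10% reduction in the gasless vNOTES group was considered to be statistically significant". With 80% power, a "one-sided α significance level of 0.05" and 1:1 allocation, the result is 49 per arm, raised to 60 for dropout.
- **Outcome measures** (and the Abstract): "The primary outcome is vital signs at the different time points", that is, T0 to T7. Ten secondary outcomes follow. The share of patients beyond a 20% blood pressure change is not among them.
- **Background:** the primary outcome is changes in MAP and heart rate during surgery. The hypothesis is that "hemodynamic profiles will be changed less during gasless vNOTES".
- **Statistical methods:** "Data from the primary outcome will be presented as mean ± standard deviation if normally distributed, and t-test will be conducted"; otherwise medians with a nonparametric test. Chi-square or Fisher tests are assigned to categorical data in general. The significance level is 0.05, with no sidedness.

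**The concern.** The sizing endpoint, the primary outcome and the primary test do not match. The first is a proportion at one moment, tested one-sided. The other two concern continuous MAP and heart rate over eight time points, with sidedness unstated. A reader who sees 80% power will credit it to the primary analysis, to which it does not belong. Nor can the reader tell which result decides the trial: there are two variables and seven post-baseline times (2 × 7 = 14 comparisons), on raw values or changes, and also the responder rate on which the trial was sized.

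A second issue follows. The hypothesis and the 20% threshold both concern the size of change and name no direction. A t-test or rank test on raw values or signed change compares location, so rises in some patients can offset falls in others.

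**Working it through.** **1. The plan's own figure.** Inputs from Sample size estimation: p1 = 0.50, a 10% reduction, one-sided alpha 0.05 (z = 1.645), power 80% (z = 0.842), 1:1.

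n per arm = [1.645·√(2p̄(1−p̄)) + 0.842·√(p1(1−p1) + p2(1−p2))]² / (p1−p2)²

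- Absolute reading, p2 = 0.40, p̄ = 0.45: (1.645 × 0.7036 + 0.842 × 0.7000)² / 0.01 = **305**. Two-sided: 388.
- Relative reading, p2 = 0.45: 1233 one-sided.
- Fall *to* 10%, p2 = 0.10: 16.

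None gives 49. Solving backwards, 49 per arm gives 80% one-sided power when p2 is about 0.26. That rate is back-solved and appears nowhere in the article.

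**2. Power of the proportion test at 49 per arm.** Power = Φ{[(p1−p2)√n − z·√(2p̄(1−p̄))] / √(p1(1−p1) + p2(1−p2))}

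| Rates | One-sided | Two-sided |
|---|---|---|
| 50% vs 40% | Φ(−0.653) = 26% | Φ(−0.970) = 17% |
| 50% vs 26% (back-solved) | Φ(0.828) = 80% | Φ(0.503) = 69% |

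With all 60 per arm evaluable, 50% vs 40% gives 29% and 19%.

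**3. Power of the planned continuous comparison.** The article gives no SD or target difference, so only the detectable standardised difference can be found: d = (1.960 + 0.842)·√(2/49) = **0.57 SD** two-sided (0.50 one-sided). At 60 per arm it is 0.51 (0.45). For an assumed 5 mmHg difference, two-sided power at 49 per arm is 87%, 70%, 54%, 38% and 24% for SDs of 8, 10, 12, 15 and 20 mmHg.

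**4. Does the t-test address smaller change?** These are illustrations, assuming normal percent change and 50% vs 26% of patients beyond ±20%, with 49 per arm.

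- *Centred on zero in both arms.* The SDs are 20/z(0.75) = 29.65 and 20/z(0.87) = 17.76. In simulation, a t-test on signed change rejects about 5% of the time, which is its alpha. If the traditional arm's mean is moved up by 5 or 10 points, power is about 16% or 51%.
- *Same data, absolute change.* The means are 0.798 × 29.65 = 23.66 and 0.798 × 17.76 = 14.17. The SDs are 0.603 × 29.65 = 17.87 and 0.603 × 17.76 = 10.71. The difference is 9.49 with standard error √[(17.87² + 10.71²)/49] = 2.98. Power is about Φ(9.49/2.98 − 1.96) = 89%.
- *Both arms rise, equal SDs.* At SD 10 the means are 20.0 and 13.6 (d = 0.645), and two-sided t-test power is 88%. At SD 15 the means are 19.9 and 9.1 (d = 0.716), and power is 94%. The two-sided proportion test has 69%.

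So on the same rates a t-test ranges from useless to better than the proportion test, depending on scale and direction.

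**5. Time point.** The pilot rate was taken as insufflation began. Under Surgical technique, gas follows the vaginal incision and port insertion. The recorded times are incision (T3) and 10 minutes later (T4), so the start of insufflation is not one of T0 to T7.

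**The case against.** A reader might infer that the planned t-test cannot test the hypothesis at all. The article does not support that. The near-5% rejection rate needs change centred on zero in both arms, whereas the Discussion expects pneumoperitoneum to raise heart rate and blood pressure. If both arms move in that direction, a comparison of means does address the hypothesis and can have more power than the proportion test. Statistical methods also leaves open whether raw values, signed change or absolute change is tested, and absolute change would test it directly. An article may leave that detail to the full protocol. The limitation is therefore conditional. It is a real possibility, because the anaesthesia section provides for MAP moving both ways.

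A reader might also infer that the proportion test is adequately powered, so that making it primary settles the matter. That holds only at the back-solved 26%, and only one-sided.

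Nor is the proportion without any test: the general chi-square or Fisher clause would cover it if it were reported. It is simply not tied to the primary outcome.

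Condensation does not explain the mismatch itself. The article states the sizing endpoint, the primary outcome and the primary test, and they disagree.

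**Conclusion.** The mismatch stands on the text alone and needs no assumption: the 80% power belongs to a proportion that is not a listed outcome, and the primary analysis as planned has no stated power. The sizing is also not supported on its own inputs. At 50% versus 40% (the absolute reading of the 10% reduction), 49 per arm gives about 26% power one-sided and 17% two-sided. For a single continuous measure the sample gives 80% two-sided power at about 0.57 SD; whether that is enough cannot be judged without an SD. The concern about smaller change holds only if raw values or signed change are tested and the arms do not move in the same direction. The figures in step 4 rest on normality and the back-solved 26%, and they show a range, not an expected result. This should be settled before analysis, because it decides which result the trial reports as primary.

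**What to change.** Before database lock:

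1. Name one primary variable, one scale (for example absolute percent change from T0, or the proportion beyond 20%) and one recorded time point after exposure begins. Say which recorded time stands for the pilot's moment.
2. Tie the matching test to it, with an effect estimate and 95% CI, and make the other MAP and heart rate profiles secondary.
3. Align the Abstract, Background, Outcome measures, Sample size estimation and Statistical methods, and update the registry entry.
4. Restate the power that the fixed sample delivers, with the same sidedness as the analysis. For the proportion, give the figures for 50% vs 40% alongside the difference at which 80% is reached. For a continuous measure, give the detectable difference (about 0.57 SD at 49 per arm, two-sided) with a sourced SD.

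The cost is wording and a registry update. No new data are needed if a recorded time point is used. The downside is that the stated power becomes less favourable. Keeping the proportion as primary with 80% power at 50% vs 40% would instead take about 305 per arm one-sided or 388 two-sided.

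### The 49 patients per arm at 80% power do not follow from the protocol's own sizing inputs under any plain reading of the 10% reduction

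*Protocol article*

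**What the plan says.** The Sample size estimation section of the protocol article bases the trial's size on the share of patients whose blood pressure changes by more than 20%. From a pilot study it takes the traditional-arm rate: "50% of patients had a greater than 20% change in blood pressure at the beginning of the CO_2_ pneumoperitoneum". The effect is given in one sentence: "The 10% reduction in the gasless vNOTES group was considered to be statistically significant". The error rates follow: "A statistical power of 80% and a one-sided α significance level of 0.05 were used for power analysis with 1:1 allocation". The result is "A sample size of 49 patients in each arm was estimated", and the final step is "Considering a dropout rate of 20%, 60 patients for each group were enrolled".

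The section gives no event rate for the gasless arm, does not say whether the 10% is absolute or relative, and names no formula.

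The Statistical methods section specifies a t-test or a non-parametric test for the primary outcome, and chi-square or Fisher tests for categorical data. Its threshold is a P "value < 0.05 was considered significant", with no direction given.

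**The concern.** The article prints its inputs and its answer side by side, so the calculation can be checked directly. With a control rate near 50%, a 10-point difference needs several hundred patients per arm at 80% power, so 49 looks far too small.

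This paragraph is the only justification given for the trial's size. A reader who takes it at face value will believe the trial has an 80% chance of detecting a 10-point fall in the proportion with a large blood pressure change. If that is untrue, a null result on this proportion could be read as evidence against a benefit the trial had little chance of showing.

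**Working it through.** **Inputs, all from Sample size estimation.** Control rate p1 = 0.50; one-sided alpha 0.05 (z = 1.645); power 80% (z = 0.842); 1:1 allocation; stated n = 49 per arm; 20% dropout; 60 per arm enrolled. The gasless rate p2 is not given, so each plain reading of the 10% is tried.

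**Formula** (pooled-variance comparison of two proportions, with p̄ = (p1 + p2)/2):

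n per arm = [1.645·√(2p̄(1−p̄)) + 0.842·√(p1(1−p1) + p2(1−p2))]² / (p1−p2)²

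**Attempt to reproduce 49.**

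- Absolute reading, 0.50 vs 0.40: [1.645·√0.495 + 0.842·√0.490]² / 0.10² = (1.157 + 0.589)² / 0.01 ≈ 305.0, so **305**.
- Relative reading, 0.50 vs 0.45: [1.645·√0.49875 + 0.842·√0.4975]² / 0.05² = (1.1616 + 0.5936)² / 0.0025 ≈ 1,232.4, so **1,233**.
- Fall to 10%, 0.50 vs 0.10: [1.645·√0.42 + 0.842·√0.34]² / 0.40² = (1.066 + 0.491)² / 0.16 ≈ 15.1, so **16**.

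The choice of formula does not explain the gap. For 0.50 vs 0.40 one-sided, unpooled variance gives 303, the arcsine method 305 and a continuity correction 325. For 0.50 vs 0.10 the continuity correction gives 20. A two-sided 0.05 test raises 305 to 388.

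**Power actually available at 49 per arm.**

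Power = Φ{[|p1−p2|·√n − z_α·√(2p̄(1−p̄))] / √(p1(1−p1) + p2(1−p2))}

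For 0.50 vs 0.40 one-sided: (0.10·7 − 1.157)/0.700 = −0.653, so power is 25.7%. Two-sided, with z = 1.960: (0.700 − 1.379)/0.700 = −0.970, so power is 16.6%.

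| Reading of 10% | p2 | n needed, one-sided | Power at 49, one-sided | Power at 49, two-sided |
|---|---|---|---|---|
| Absolute | 0.40 | 305 | 25.7% | 16.6% |
| Relative | 0.45 | 1,233 | 12.5% | 7.1% |
| Down to 10% | 0.10 | 16 | 99.9% | 99.6% |

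If all 60 per arm were evaluable, one-sided power for 0.50 vs 0.40 would still be only 29.2%.

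**What 49 does correspond to.** Solving the power formula for p2 at n = 49 and 80% power gives p2 = 0.259 one-sided (a fall of about 24 points) and 0.231 two-sided (about 27 points). Run forwards one-sided, p2 = 0.25 needs 46 per arm and p2 = 0.26 needs 50, so 49 lies between them.

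**Dropout step.** 49/(1 − 0.20) = 61.25, so 62 per arm would preserve 49. The planned 60 leaves 60 × 0.80 = 48. One-sided power for 0.50 vs 0.40 moves from 25.7% to 25.4%, which is negligible. The detectable rates at 48 are 0.257 one-sided and 0.228 two-sided, still about 26% and 23%.

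**The case against.** The strongest reply is that the mistake may lie in the reported effect rather than in the calculation. Since 49 fits about 50% vs 26%, the sponsor may have assumed a much larger effect and described it badly. This stands as a possibility, and the document cannot settle it. It does not rescue the paragraph, because then the printed effect is wrong. A condensed article may leave details out, but here the inputs and result are printed and conflict.

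Three stronger conclusions are tempting and are not supported.

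- A reader might infer that the design simply has 26% power and will miss its target three times in four. That holds only if the 10% is absolute. Power is 12.5% on the relative reading and 99.9% if the rate falls to 10%.
- A reader might infer that the primary analysis is underpowered. The primary outcome is vital signs at T0 to T7, compared by t-test or a non-parametric test, and the article gives neither a standard deviation nor a target mean difference. For orientation, 49 per arm with a two-sided 0.05 t-test has 80% power for about 0.57 standard deviations. Whether that is adequate cannot be judged from the document.
- A reader might infer that a one-sided sizing contradicts a two-sided analysis. Statistical methods gives no direction, so the two-sided figures are conditional on the usual convention.

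The dropout shortfall is also too small to carry weight: 49 × 1.2 = 58.8, so 60 is consistent with a common shortcut.

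**Conclusion.** The sample size statement is wrong as written. From the stated inputs, 80% power requires 305, 1,233 or 16 per arm depending on how the 10% is read, and none is near 49. On the natural absolute reading the requirement is about six times the stated figure (305/49 ≈ 6.2). Power for the binary endpoint is then about 26% one-sided, or about 17% if tested two-sided, against the 80% claimed.

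The failure to reproduce 49 does not depend on choosing among these readings. The 26% and 17% figures do: they assume an absolute 10-point fall, a 50% control rate, and a comparison of the proportions with a blood pressure change above 20%. That 49 reflects an assumed gasless rate near 26% is an inference from the arithmetic, not something the protocol says.

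**What to change.** Keep N = 120 and rewrite the Sample size estimation paragraph.

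1. State the gasless-arm rate actually assumed, whether the 10% is absolute or relative, and the formula used.
2. Delete the claim of statistical significance attached to the 10%. Significance is a property of a result, not of a design assumption.
3. Use the same sidedness for sizing and analysis, and state it in Statistical methods.
4. Present the power claim as a detectable difference, on these lines: with 48 to 49 evaluable patients per arm, the trial has 80% power to detect 50% vs about 26% (one-sided 0.05) or about 23% (two-sided 0.05) with a blood pressure change above 20%; power for a 10-point reduction is only about 26% or 17% respectively. Label this as what the existing size can detect, not as the assumption originally made. Keep the term blood pressure, since the sizing section does not specify MAP.
5. Note that 60 per arm leaves 48 evaluable at 20% dropout.

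The cost is one rewritten paragraph, a stated test direction in Statistical methods and a registry update, with no extra patients. The price is a less favourable stated effect: a fall of about 24 to 27 points instead of 10.

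### The stated 49 patients per arm does not give 80% power for the stated 10% reduction from 50%: a 10-point fall needs about 305 per arm, and 49 per arm has about 26% power

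*Protocol article*

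**What the plan says.** The calculation is in the Sample size estimation section of the protocol article. It rests on a binary quantity, whether a patient's blood pressure changes by more than 20%.

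- Traditional arm, from a pilot study: "50% of patients had a greater than 20% change in blood pressure at the beginning of the CO_2_ pneumoperitoneum".
- Gasless arm, direction only: "We assume that the number of patients with a blood pressure change of more than 20% is less in the gasless vNOTES group".
- Size of the effect: "The 10% reduction in the gasless vNOTES group was considered to be statistically significant".
- Error rates and allocation: "A statistical power of 80% and a one-sided α significance level of 0.05 were used for power analysis with 1:1 allocation".
- Result: "A sample size of 49 patients in each arm was estimated".
- Allowance for losses: "Considering a dropout rate of 20%, 60 patients for each group were enrolled".

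The section gives no gasless-arm rate, no formula, and no mean difference or standard deviation.

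**The concern.** The section sets its inputs and its result side by side, so the result can be checked. A 10-point difference around 50% is a small effect for a binary endpoint and normally calls for several hundred patients per arm, so 49 looks far too few.

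This calculation is the only numerical support for the trial's size. If it is wrong, the design lacks the power claimed for it, and a reader cannot tell what effect the trial was built to detect. A non-significant comparison could then be taken as evidence of no haemodynamic advantage when the trial had little chance of showing one of the stated size.

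The effect sentence has a second fault. Statistical significance is a property of observed data. It cannot be assigned in advance to an assumed difference.

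**Working it through.** **Inputs, all from Sample size estimation.** p1 = 0.50; power 80% (z = 0.842); one-sided alpha 0.05 (z = 1.645); 1:1 allocation. The gasless rate p2 must be inferred from the 10% reduction.

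**Formula.** With d = p1 − p2 and p̄ = (p1 + p2)/2,

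n per arm = [1.645·√(2p̄(1−p̄)) + 0.842·√(p1(1−p1) + p2(1−p2))]² / d²

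**Step 1: try to reproduce 49.**

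*Absolute reading, 50% to 40%.* p̄ = 0.45, so the first term is 1.645·√0.495 = 1.157 and the second is 0.842·√0.490 = 0.589. Then n = (1.157 + 0.589)²/0.01 ≈ 305.

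The other readings, by the same formula and with two variants:

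| Reading of the 10% | p2 | Pooled | Unpooled | Continuity-corrected |
|---|---|---|---|---|
| Absolute fall | 0.40 | 305 | 303 | 325 |
| Relative fall | 0.45 | 1,233 | 1,231 | 1,273 |
| Gasless rate itself 10% | 0.10 | 16 | 14 | 20 |

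The arcsine method also gives 305 for the absolute reading. A two-sided 5% test moves the absolute reading to 388. A one-sample test of 40% against 50% gives 153. None of these is near 49.

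**Step 2: what 49 per arm corresponds to.** Solving the formula for p2 at n = 49 gives p2 ≈ 0.259. Check: p̄ = 0.3795, the terms are 1.129 and 0.560, and (1.129 + 0.560)²/0.241² ≈ 49. The unpooled form gives p2 ≈ 0.263. The implied fall is therefore about 24 points. At n = 60, p2 ≈ 0.280, a fall of 22 points.

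**Step 3: power for 50% against 40%.** Power = Φ[(d − 1.645·SE₀)/SE₁], with SE₀ = √(2p̄(1−p̄)/n) and SE₁ = √((p1(1−p1) + p2(1−p2))/n).

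- n = 49: SE₀ = 0.1005 and SE₁ = 0.1000, so (0.1 − 0.1653)/0.1000 = −0.65 and power is 25.7%.
- n = 60: SE₀ = 0.0908 and SE₁ = 0.0904, so (0.1 − 0.1494)/0.0904 = −0.55 and power is 29.2%.

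Exact calculation gives 24% and 31% for the z-test, and 19% and 26% for Fisher's test. For 50% against 45%, power is 12.5% at 49 per arm and 13.6% at 60.

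**Step 4: would an observed 10-point difference be significant?** For 50% against 40%, z = 0.1/SE₀.

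- 49 per arm: z = 0.1/0.1005 = 0.99, one-sided P ≈ 0.16.
- 60 per arm: z = 0.1/0.0908 = 1.10, one-sided P ≈ 0.14.

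With an uncorrected one-sided z-test and about half the traditional arm having the event, the first result to pass 0.05 at 60 per arm is 30 against 21 events (15 points, P = 0.048). At 49 per arm it is 24 against 15 events (18 points, P = 0.032); 24 against 16 just misses, at P = 0.0501. Fisher's test is stricter: 30 against 21 of 60 gives one-sided P = 0.070.

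**The case against.** Four points can be made for the plan.

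- **The primary analysis is not this binary comparison.** Outcome measures names vital signs at T0 to T7, and Statistical methods plans a t-test or a non-parametric test. The 26% is therefore the power of the sizing calculation as written. It is not the power of the planned primary analysis, which cannot be worked out without a mean difference and standard deviation. This limit stands. It does not rescue the 80%, because the binary calculation is the only basis given for that figure.
- **The 10% is ambiguous.** The article does not say whether it is absolute or relative, and does not call it clinically important. That is true, but of the two kinds of reduction the absolute one is kinder to the plan; the relative one needs about four times as many patients (1,233/305 ≈ 4).
- **A 10-point difference could be significant elsewhere on the scale.** With 6 of 60 against 0 of 60, Fisher's one-sided P is 0.014. The remark on significance therefore holds only near the 50% control rate that the plan assumes.
- **An article condenses a fuller document.** A missing formula could be excused on that ground. A result that contradicts the inputs printed beside it cannot.

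The 49 may come from an effect that the article does not state. A one-sided comparison of means with a standardised difference of 0.5 needs about 50 per arm, for example. That is speculation, since the section describes a proportion.

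**Conclusion.** The concern holds. The stated inputs and the stated 49 per arm contradict each other. On the absolute reading the requirement is about 305 per arm, roughly six times as many (305/49 ≈ 6.2), so neither rounding nor the choice of formula explains the gap. Power for 50% against 40% is about 26% at 49 per arm, and about 29% even if all 60 per arm are evaluable. If that were the true effect, a one-sided test of this binary endpoint would miss it about three times in four at 49 per arm. The design has 80% power only for a fall of about 24 points at 49 per arm, or 22 points at 60.

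These figures assume a 50% control rate, one-sided 5% alpha, equal arms and a two-proportion comparison, all as the article states. They describe the sizing calculation and make no claim about the power of the t-test on continuous vital signs.

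**What to change.** Correct the Sample size estimation section and leave the sample size as it is.

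1. State the gasless-arm rate actually entered, its source and the formula used.
2. If 49 per arm stands, say that it gives 80% power at one-sided 5% for a fall from 50% to about 26%. If the authors cannot show that this rate was assumed in advance, label it as back-solved from the sample size. Add that power for a fall to 40% is about 26% with 49 per arm and 29% with 60.
3. Remove the claim that the 10% reduction is statistically significant. Call it the assumed difference, or the clinically relevant one if the authors can justify that, and say whether it is absolute or relative.
4. State that a non-significant comparison of these proportions is inconclusive for reductions below about 22 to 24 points, and report the between-arm difference with its confidence interval.
5. While editing, correct the dropout step: 49/(1 − 0.20) = 61.25, so 62 per arm, whereas 60 per arm with 20% lost leaves 48.

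The cost is a rewritten paragraph, plus the registry entry if it repeats the calculation. No extra patients are needed. The drawback is a much less favourable stated power for a 10-point effect.
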